## Abstract

**Background:**

Depression is a prevalent disorder in chronically ill elderly persons. It may decrease quality of life, and increase functional disability, medical costs, and healthcare utilisation. Because patients may slip into a downward spiral, early recognition and treatment of depression is important. Depression can be treated with antidepressants or psychological interventions; the latter can also be applied by trained paraprofessionals.

In this paper, we describe the design of the DELTA study (Depression in Elderly with Long-Term Afflictions). The first objective of the DELTA study is to evaluate the effectiveness and cost-effectiveness of a minimal psychological intervention (MPI) to reduce depression in chronically ill elderly patients. The second objective is to evaluate whether a potential effect of the MPI may differ between types of chronic illnesses. The tailor-made intervention is administered by nurses, who are trained in the principles of cognitive behavioural therapy and self-management.

**Methods/Design:**

DELTA is a two-armed randomised controlled trial, comparing MPI to usual care. A total number of 180 patients with diabetes mellitus type II (DM) and 180 patients with chronic obstructive pulmonary disease (COPD), who in addition suffer from non-severe depression, will be included in the study. In our study, non-severe depression is defined as having minor depression, mild major depression or moderate major depression. The primary outcome measure is depression using the Beck Depression Inventory. Secondary outcome measures include quality of life, daily functioning, self-efficacy, autonomy, and participation. In the economic evaluation, cost-effectiveness and cost-utility ratios will be calculated. Furthermore, a process evaluation will be carried out.

Analyses will include both univariate and multivariate techniques and according to the intention to treat principle. The economic evaluation will be done from a societal perspective and data of the process evaluation will be analysed using descriptive techniques.

**Discussion:**

A total number of 361 patients has been included in the study. All interventions have been administered and follow-up data will be complete in September 2006.

Preliminary results from the process evaluation indicate that patients' satisfaction with the intervention is high. If this intervention proves to be effective, implementation of the DELTA intervention is considered and anticipated.

## Background

Depression is a prevalent and disabling disorder, especially in patients with chronic illnesses, such as diabetes mellitus type II (DM) and chronic obstructive pulmonary disease (COPD). In older patients with DM, prevalence rates of clinical relevant depression range from 14 to 17% [1,2]. In older patients with COPD, prevalence rates of 25% for minor depression have been reported [3]. Prevalence rates of major depression in older COPD patients range from 6 to 42% [4].

Persons suffering from minor or major depression have increased mortality risks and a decreased quality of life compared with non-depressed persons [5-7]. Furthermore, depression has been shown to increase health care utilisation [8,9], medical costs [10], and disability [8,9,11]. Since disability predicts the onset of depression and depression itself may further heighten risks of a progressing disability, this process of mutual reinforcement may lead to a downward spiral [11-14]. In addition, depression impairs one's ability to adhere to disease management regimens (diet, exercise, quitting smoking, taking medication regularly), potentially worsening the course of the chronic illness [15,16]. Hence, an early detection of depressive symptoms and treatment of depression is important in chronically ill elderly persons, thereby preventing or breaking a downward spiral. In primary care however, depression often remains undetected [17]. General practitioners have limited time and furthermore, current Dutch guidelines for DM and COPD don't take into account the psychological consequences of the chronic illness.

Available treatment options are antidepressants or psychological interventions. The effectiveness of antidepressants has been extensively studied and proven in major depression [18]. Since there is no clear evidence of the effectiveness of antidepressants in minor depression [19,20], clinical guidelines advise against using antidepressants in minor depression [21,22]. Cognitive therapy (CT) seems to be as effective as antidepressants in severe depression [23], and also in patients with mild and moderate depression [24]. Furthermore, CT seems to have an enduring effect [25]. It is also increasingly recognised that chronically ill elderly suffering from depression might benefit from psychosocial support and improving coping skills, such as self-management techniques [21,26]. In a study with DM type II patients, cognitive behavioural therapy (CBT) in combination with supportive diabetes education proved to be an effective treatment for major depression [27]. Similarly, self-management strategies in COPD patients have been reported to improve the patients' health status and to reduce hospital admissions [28].

Accumulating evidence shows that primary care staff can be trained in psychological interventions for depression [29]. Several studies reported that practice nurses can successfully administer interventions to reduce depression in primary care settings [30,31].

We developed a minimal psychological intervention (MPI), based on principles of self-management and CBT. The intervention is administered by nurses and aims to reduce non-severe depression in chronically ill elderly persons. Findings of a prior smaller pilot study showed that the intervention was feasible and acceptable to patients. Furthermore, the training programme, developed to teach nurses to administer the intervention, appeared to be feasible, attractive and successful among nurses [32].

In this contribution, we present the design of the DELTA study (Depression in Elderly with Long-Term Afflictions). The first objective of this randomised controlled trial (RCT) is to evaluate the effectiveness and cost-effectiveness of an MPI that is administered by a nurse and aims to reduce non-severe depression in chronically ill elderly patients. The effects of the MPI are compared with usual care. The second objective is to evaluate whether a potential effect of the MPI is different between types of chronic illnesses.

## Design and methods

### Design

The DELTA study is a two-armed randomised controlled trial, in which an effect evaluation, an economic evaluation and a process evaluation will be carried out. A total number of 360 patients will be included, 180 of which are patients with DM and 180 are patients suffering from COPD. We chose DM and COPD because first, they are highly prevalent in primary care. Second, they have a different course and prognosis. DM can be seen a gradual progressive illness, whereas COPD as a gradual relapsing condition [33]. This difference enables us to test whether the intervention is potentially generic. Approval for conducting this study was granted by the Medical Ethics Committee of the Maastricht University/Academic Hospital Maastricht.

### Setting and recruitment

In general practices in the southern part of Limburg, a province in the south of the Netherlands, all patients of 60 years and over with DM and or COPD were selected by the general practitioner, the general practitioner's assistant, or the research assistant. Selection was made using ICPC codes (T90, R91.01, R95, R99.06) if possible and otherwise by medication prescriptions (those drugs which are most often prescribed by the general practitioner for these chronic illnesses). In the last phase of patient selection, the general practitioner applied the inclusion and exclusion criteria using a pre-coded form with checkboxes for each criterion (Table 1).

All selected patients received a letter from their general practitioner with a request to complete a short screening questionnaire. This questionnaire, the Patient Health Questionnaire-9 (PHQ-9), consists of nine questions regarding the prevalence of symptoms of depression over the last two weeks. The response options are: "Not at all", "Several days", "More than half the days" and "Nearly every day". Its brevity and the fact that it is a self-administered questionnaire make it a useful tool in screening for depression in primary care. The PHQ-9 has been validated for both diagnosing depression and measuring severity [34-36]. Five questions on demographic variables were included in the questionnaire. Patients received a reminder by telephone two weeks after the questionnaire had been sent.

All patients who scored at least 2 depressive symptoms at least at "more than half the days" and at least one of these symptoms was depressed mood or anhedonia, were invited to participate in an interview to confirm or reject the diagnosis of depression.

The Mini International Neuropsychiatric Interview (MINI) was used to confirm the diagnosis from the PHQ-9. The interview took place at the patient's home and was administered by a trained nurse. The MINI is a validated and reliable diagnostic structured interview, covering 17 disorders based on DSM-IV criteria [37,38]. An extra diagnosis box for minor depression was added to the MINI, based on the research criteria for minor depression as described in the DSM-IV [39]. Furthermore, the Hamilton Depression Rating Scale (HDRS) was used to determine the severity of the depression [40,41]. Patients were excluded if they met one of the following criteria: if the MINI indicated a major depression in combination with a score above 18 (indicating a severe depression) on the HDRS, if the MINI indicated suicidal risk, or if the MINI indicated no depression at all (Table 1). Patients with a major depression and/or suicidal risk were referred back to their general practitioner. All remaining eligible patients (patients with a minor depression, non-severe major depression, or dysthymia) were invited to participate in the study and to give their informed consent.

### Randomisation

After having signed the informed consent form, patients enrolled in the study and filled in the baseline questionnaire. After having completed the baseline questionnaire, patients were assigned to either the intervention or control group. Randomisation was performed by an external agency using a computerized random number generator. In order to avoid an imbalance of chronic illness and general practice (care level) over the two groups, stratification for general practice and chronic illness (DM or COPD) was performed. Furthermore, to obtain equal numbers in both arms, a blocked design with a block size of two was applied. The intervention group received a Minimal Psychological Intervention, while the control group received usual care as given by their general practitioner, according to the guidelines for the specific chronic illness.

### Minimal Psychological Intervention

The intervention was given by a trained nurse, at the patient's own home. During a period of at most three months, patients received a maximum of 10 visits from the nurse. The number of visits depended on the patient's progress.

The Minimal Psychological Intervention contains elements from the Chronic Disease Self-Management Program (CDSMP) by Lorig and Gonzales [42], the Reattribution model from Goldberg [43] and from the work of the project group of the Interventie Studie Eerste Lijn (INSTEL) [44], as previously described [32]. The intervention aims at teaching patients to take responsibility for day-to-day management of their illness and its consequences. In short, it consists of five phases:

Phase 1. The nurse explores the patient's cognitions on the origin of symptoms and complaints, and their relation to limitations and behaviour.

Phase 2: The patient keeps a diary, where he or she records symptoms, complaints, thoughts, worries, related feelings, and behaviour.

Phase 3: Using information from the diary, the nurse challenges the patient to link his or her mood and consequent behaviour to the course of the chronic illness. A distinction will be made between complaints related to the illness itself, and those related to the emotional and behavioural consequences of the illness.

Phase 4: Introduction of the self-management approach by the nurse. The patient explores his or her possibilities to alter his or her behaviour. He or she then makes a plan on how to solve perceived problems and sets specific goals to be reached before the next visit from the nurse.

Phase 5: Evaluation of the progress in achieving the goals.

After a patient has completed these five phases successfully, he or she is supposed to be able to apply the self-management approach to any situation or problem he or she may encounter in the future. In consultation with the patient, the nurse can then decide to conclude the series of intervention visits.

### The training program for nurses

#### Administering the MINI

In an 8 h session, the nurses were trained how to confirm a diagnosis of depression by using the MINI and HDRS by a psychiatrist.

#### Applying the Minimal Psychological Intervention

During three 8 h sessions, with 2-week intervals, four nurses were trained by two experienced trainers (a psychologist/cognitive behaviour therapist, and a general practitioner) on how to apply the intervention. In between training days, nurses practised their newly learned skills on a pilot patient. As mentioned earlier, the training program has been shown to be feasible, attractive and successful among nurses [32]. Booster sessions were being held regularly during the study, and both a psychiatrist and a psychologist could be contacted by telephone to discuss cases at any time.

### Data collection

Data was collected at five points in time: at baseline (T0), one week after the intervention period (T1), and at three, six and nine months after the intervention period (T2, T3, T4) (Fig. 1). The intervention period for patients allocated to the intervention group varies from one week to three months. The intervention period of the control group is fixed at six weeks, which is estimated to be the mean duration of the intervention period in the intervention group. Data were collected using self-administered questionnaires and cost diaries in combination with interviews by telephone.

### Effect evaluation

Table 2 provides an overview of the measures of the effect and economic evaluation, and time of assessment.

#### Primary outcome measures

The primary outcome measure in this study was level of depression, measured with the Beck Depression Inventory (BDI) [45,46]. The BDI consists of 21 items measuring symptoms of depression and has proven to be a valid and reliable tool [47].

#### Secondary outcome measures

Secondary outcome measures in the study were: Quality of life measured with the Short Form-36 (SF-36) [48], disease-specific quality of life assessed with the Problem Areas in Diabetes questionnaire (PAID-1) [49] for diabetes patients, and the St. George's Respiratory Questionnaire (SGRQ) for patients with pulmonary disease [50,51]. Furthermore, daily functioning was assessed with the Activities of Daily Life scale (ADL) from the Groningen Activity Restriction Scale (GARS) [52], self-efficacy assessed using the 12-item Self-efficacy scale [53,54] and autonomy and participation using the questions from the domain Autonomy outdoors from the Impact on Participation and Autonomy questionnaire (IPA) [55,56].

#### Covariates

Additionally, information on possible confounding factors and effect modifiers was collected. Information on demographic factors (age, gender, marital status, religion, education, occupation) was collected in the screening phase. Other factors measured are: coping using the active coping, avoidant coping and passive coping scales from the Utrecht Coping List (UCL) [57], mastery using the Personal Mastery Scale developed by Pearlin and Schooler [58], anxiety assessed using the anxiety subscale from the Symptom Checklist (SCL-90) [59], social support using the short version of the Social Support List- Interactions questionnaire (SSL-I) [60,61], co-morbidity using the Chronic conditions list from Statistics Netherlands (CBS – Centraal Bureau voor de Statistiek), life events using a list of 16 life events where patients report which life events they have experienced in the past year, and how they value these events (positive, negative, or neutral). Personality was measured using scales for neuroticism and extraversion from the Eysenck Personality Questionnaire (EPQ) [62]; severity of the chronic illness was assessed using the St. George's Respiratory Questionnaire (SGRQ) for COPD patients [50,51], and the Diabetes Symptom Checklist – Revised (DSC-R) for diabetes patients [63]. If possible, severity of the chronic illness will also be assessed by retrieving lung function (FEV_1_) and/or blood glucose levels (Hba1c) from hospital records or the general practitioner's records at the end of the study Finally, smoking and body mass index (BMI) were assessed, and in order to check for contamination in the control group, two questions to check whether or not the patients in the control group had heard or benefited from the intervention were added to the questionnaire. Contamination of the control group may lead to a smaller difference in effect between intervention and control group.

### Economic evaluation

A combined cost-effectiveness/cost-utility analyses will be performed from a societal perspective. The BDI is used as primary outcome measure in the cost-effectiveness analyses. The primary outcomes measure for the cost-utility measure will be utilities based on the social tariff of the EuroQol [64]. Healthcare costs, patient and family costs, as well as productivity losses will be recorded using cost diaries [65]. Patients prospectively kept the diary for two weeks at baseline and for four weeks at each follow up measurement. Afterwards, a telephonist contacted them to retrieve the information from the diary. Data were immediately entered in a computer file to ensure efficiency and reliability. The costs of the intervention were separately calculated. For the valuation of health care costs and patient and family costs, the updated Dutch Guideline for costing in economic evaluations [66] will be used. If no guideline costs existed, cost prizes were estimated using real costs and tariffs. For future costs and effectiveness data, a discount rate of 4% will be used.

### Process evaluation

A process evaluation was carried out to assess the following outcomes. The reach of the intervention, defined as the proportion of the intended target population that actually participated in the intervention. The dose delivered was defined as the completeness of the intervention and number and duration of the intervention visit. Dose received, described in two concepts, namely exposure and satisfaction. Exposure is the extent to which patients actively engage with and are receptive to the intervention, and satisfaction is defined as patient's satisfaction with the intervention [67]. Barriers were described as the extent in which problems were encountered during the intervention.

Data were collected using questionnaires filled out by nurses after every intervention visit, by means of checklists that were kept by the nurse for every patient to report which steps of the intervention had been taken, and by questionnaires filled out by patients after finishing the intervention.

### Analysis

Data will be analysed according to the intention to treat principle. In addition, on treatment analyses will be performed. Changes in primary and secondary outcome measures between intervention and control group will be analysed using both univariate and multivariate techniques. Models will be adjusted for age, gender and socio-economic status (SES), and baseline differences. Potential additional confounding factors and effect modifiers will be checked and, if necessary, included in the model. Since dependency between observations of subjects from the same general practice may exist as well as between repeated observations within persons, multilevel analyses will also be carried out.

All analyses will be performed for intervention and control group in total, as well as for DM and COPD separately.

In the economic evaluation the cost and effects of care as usual and MPI by a practice nurse will be calculated and compared. The cost-effectiveness ratio will be stated in terms of costs per improvement on the BDI, the cost-utility ratio will focus on the net cost per QALY gained. Ratios will be determined for the total patient population as well as for COPD or DM patients separately. Bootstrapping will be used to estimate confidence intervals for calculated ratios.

Descriptive statistics, Chi-square and t-tests will be used to analyse data from the process evaluation.

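### The planned on-treatment analysis rests on exposure that depends on progress in the MPI arm only; a complier-average effect would estimate the effect of receiving the MPI and keep randomisation

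*Protocol article*

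**What the plan says.** The Analysis section of the protocol article sets the governing principle: "Data will be analysed according to the intention to treat principle". It then adds: "In addition, on treatment analyses will be performed". It does not say who counts as on treatment or how controls enter the comparison. Outcome models are adjusted for age, gender, socio-economic status and baseline differences, and further confounders are added if needed.

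The Minimal Psychological Intervention section describes a flexible dose: "During a period of at most three months, patients received a maximum of 10 visits from the nurse", and "The number of visits depended on the patient's progress". On ending the visits it says: "After a patient has completed these five phases successfully", the patient should be able to apply the approach unaided, and "In consultation with the patient, the nurse can then decide to conclude the series of intervention visits".

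For the other arm, the Randomisation section says that "the control group received usual care as given by their general practitioner". Data collection gives controls a fixed six-week period, against one week to three months in the MPI arm. The Process evaluation section records a nurse questionnaire after every visit and a checklist of the steps taken with each patient.

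**The concern.** An on-treatment comparison is sound only if being on treatment is unrelated to outcome, or if the relation is fully captured by the covariates. Here the article itself ties the number of visits, and the end of the series, to how the patient is doing. Visits and phases exist in one arm only, so no matching filter can be applied to usual care. The selection takes place after randomisation, whereas the named adjustments are demographic and baseline quantities.

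What is at stake is the secondary message. An on-treatment estimate printed beside the intention-to-treat estimate is easily taken as the effect of actually receiving the MPI. It would carry a selection bias of unknown sign and an uncontrolled error rate.

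**Working it through.** **Plan's own figure.** The article gives no number for the on-treatment analysis. Its sample size of 192 does reproduce: (1.960 + 1.282)² × 0.18 × 0.82 / 0.18² = 47.9, so 48 in each of four groups. That figure plays no part below.

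**Inputs.**
- From the article: four groups of 90, hence 180 per arm; α = 0.05, taken as two-sided.
- Assumed: no true effect; a share s of 0.10-0.30 of MPI patients off treatment; those patients worse on the BDI by g = 0.3-0.7 SD; all controls kept; no covariate adjustment.

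**Model 1: off-treatment patients have a worse prognosis.** With no effect, the whole MPI arm has the same mean as controls. Removing a share s that is g SD worse than the rest moves the remaining mean by s × g.

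- Bias = s × g
- SE = √[1/(180(1 − s)) + 1/180]
- Type I error = P(Z > 1.96 − bias/SE) + P(Z < −1.96 − bias/SE)

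| s | g (SD) | Bias (SD) | SE (SD) | Bias/SE | Type I error |
|---|---|---|---|---|---|
| 0.10 | 0.3 | 0.030 | 0.108 | 0.28 | 5.9% |
| 0.25 | 0.5 | 0.125 | 0.114 | 1.10 | 19.5% |
| 0.30 | 0.7 | 0.210 | 0.116 | 1.81 | 44.0% |

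A simulation of 20,000 trials of the middle case gave a bias of 0.126 SD and 19.0% rejection. The intention-to-treat test rejected in 4.8%.

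**Sensitivity of the middle case.** If adjustment removed half the gap (g = 0.25), the bias would be 0.0625 SD and the error 8.5%. With 135 analysed per arm (25% attrition, inside the article's 20-30%), the bias stays at 0.125 SD, the SE rises to 0.131 and the error falls to about 16%.

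**Model 2: selection on progress itself.** A fraction q of the MPI arm is kept according to a score that correlates ρ with the patient's own improvement. Bias = ρ × φ(z₁₋q)/q. For q = 0.8 and ρ = 0.3 this is 0.3 × 0.280/0.8 = 0.105 SD. Simulated type I errors come from 4,000 trials per case.

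| q | Bias at ρ = 0.3 (SD) | Type I error | Bias at ρ = −0.3 (SD) |
|---|---|---|---|
| 0.9 | 0.06 | 9% | −0.06 |
| 0.8 | 0.11 | 16% | −0.10 |
| 0.7 | 0.15 | 26% | −0.15 |
| 0.6 | 0.19 | 36% | −0.19 |

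Positive ρ represents a completer set. Negative ρ represents a minimum-visit set from which fast improvers drop out because their visits end early. At ρ = 0 there is no bias and the error is about 5%.

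**Complier estimate.** If controls have no access to the MPI, this is the intention-to-treat difference divided by uptake q. It showed no bias in any of these null cases, but that is by construction, since zero divided by q is zero. Its standard error is larger by 1/q: 0.105/0.8 = 0.13 SD at q = 0.8.

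**The case against.** A reader might infer that the plan sets successful completers against all controls, and so favours the MPI even when it does nothing. The documents do not support that. The sentence on the five phases says when visits may be concluded and does not define an analysis set. Nothing says that every control enters the comparison. A control-side exclusion is possible, because the questionnaire includes "two questions to check whether or not the patients in the control group had heard or benefited from the intervention". The definition may stand in the full protocol or analysis plan, which are not shown, so its absence is not held against the article. The direction is also open, as Model 2 shows.

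The size can be challenged too. The share and the gap are assumptions. A fixed prognostic gap is partly open to baseline adjustment, and the trial measures many covariates, including coping, mastery, anxiety, co-morbidity and illness severity. The sensitivity runs show that this matters. It weakens the figures without restoring the protection of randomisation, because progress under treatment is not a baseline quantity.

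The remedy has limits as well. A complier estimate adds no test of the null beyond intention to treat. A demanding uptake threshold breaks its key assumption. For example, let 75% reach the threshold and a further 15% be partly treated with half the effect d. The intention-to-treat effect is then 0.75d + 0.15 × 0.5d = 0.825d, and 0.825d/0.75 = 1.10d, which is 10% too large. The contamination items are weak exposure data, since having heard of the MPI is not receiving it.

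Finally, the on-treatment analysis is an addition, and neither the sample size nor any stated decision rule depends on it.

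**Conclusion.** The point holds in a limited form. Any on-treatment set built on visits or phases is selected after randomisation in the MPI arm. In this trial the selection is tied to progress by design, and the stated adjustment cannot be relied on to remove it. The sign of the bias depends on a definition that the article does not give.

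The size is illustrative. The range of 0.03-0.21 SD and 6-44% type I error describes a set that drops worse-off patients, under Model 1's assumed inputs. Effective adjustment would lower both figures, and attrition would lower the error rate but not the bias.

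Intention to treat governs and its conclusion is unaffected. The case for change is that a better-founded estimate of the effect of receiving the MPI is available from records already kept.

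**What to change.** Amend the Analysis section as follows.

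- As the estimate of the effect of receiving the MPI, report a complier-average causal effect on the BDI. Use randomised arm as the instrument (two-stage least squares, or the intention-to-treat difference divided by the between-arm difference in uptake), with the same covariates as the intention-to-treat model.
- Define uptake as at least one nurse visit, taken from the visit questionnaires and checklists, and fix this before outcomes are analysed. The article reports follow-up as still in progress, so at that stage this was feasible.
- Use any higher threshold, such as all five phases begun, only as a sensitivity analysis, because partly treated patients violate the exclusion assumption.
- If an on-treatment comparison is kept, state who is in it, label it descriptive and subject to selection, and give no p-value.

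The cost is a wording change and one extra model on data already collected. The downsides are a wider interval, reliance on the assumption that allocation acts only through receipt of the MPI, and no new test of the null.

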### Power calculation

Assuming an α of 0.05, a 1 – β (power) of 0.90, a decrease of 18 percent of non-severe depression in the intervention group versus zero percent in the control group, 192 persons were needed [68]; 48 COPD and 48 DM patients in the intervention group and 48 COPD and 48 DM patients in the control group. We decided to recruit four groups of 90 patients (in total: 360), as we not only anticipated the potential need for sub-group specific analyses, but also anticipated attrition varying between 20 and 30 percent (e.g. due to refusals during the follow-up).

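### The second objective asks whether the MPI effect differs between DM and COPD, but the only illness-specific analyses stated are separate ones and no between-illness contrast is named

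*Protocol article*

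**What the plan says.** The Background of the protocol article sets two objectives. The second is comparative: "The second objective is to evaluate whether a potential effect of the MPI is different between types of chronic illnesses". The Design section gives the differing course of the two illnesses as a reason for choosing them: "This difference enables us to test whether the intervention is potentially generic". The Randomisation section stratifies by illness.

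Three sentences in the Analysis section bear on this objective:

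- On effects by illness: "All analyses will be performed for intervention and control group in total, as well as for DM and COPD separately".
- On cost ratios by illness: "Ratios will be determined for the total patient population as well as for COPD or DM patients separately".
- On effect modification in general: "Potential additional confounding factors and effect modifiers will be checked and, if necessary, included in the model".

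The Analysis section also plans multilevel models to allow for practices and repeated measurements.

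The Power calculation section starts from "Assuming an α of 0.05, a 1 – β (power) of 0.90" and "a decrease of 18 percent of non-severe depression in the intervention group versus zero percent in the control group, 192 persons were needed", made up of "48 COPD and 48 DM patients in the intervention group and 48 COPD and 48 DM patients in the control group". It then raises recruitment to four cells of 90, partly for possible subgroup work and partly for 20-30% attrition. It gives no power or precision for a difference between the illnesses.

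**The concern.** The second objective concerns a difference between two treatment effects. The stated illness-specific analyses yield two effects, each tested against zero, and nothing that compares them. Significance in one illness but not the other is not evidence that the effects differ. Significance in both is not evidence that they are alike.

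The effect-modifier sentence does not fill the gap. It refers to unnamed additional factors, names neither illness nor a model term, and makes inclusion in the model conditional.

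At stake is the reading of one of only two objectives. With no contrast named, the article leaves open that a claim of benefit in one illness only, or of a generic effect, might rest on two separate p-values. The overall comparison of MPI with usual care is not affected.

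**Working it through.** **1. Reproducing the stated sample size.** Inputs from Power calculation: α 0.05 (sidedness not stated; two-sided assumed), power 0.90, 18% against 0%. With the unpooled variance,

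n per arm = (1.960 + 1.282)² × (0.18 × 0.82) / 0.18² = 47.87, so 48.

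Two arms in each of two illnesses give 4 × 48 = 192, the stated figure. The sizing is thus two separate within-illness comparisons of 48 against 48. It does not address the difference between illnesses.

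**2. Patients per cell (illness by arm).** 360/4 = 90 at recruitment. After 30% attrition 90 × 0.7 = 63 remain, and after 20% attrition 90 × 0.8 = 72.

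**3. Chance that exactly one illness is significant when the true effects are equal.** The illnesses are separate strata, so with power p in each the chance is 2p(1 − p).

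*(a) The article's binary planning effect.* For the pooled two-proportion test, p = Φ{[0.18 − 1.96√(2 × 0.09 × 0.91/n)] / √(0.18 × 0.82/n)}. At n = 63 this is Φ(1.654) = 0.951, and 2 × 0.951 × 0.049 = 0.093.

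| n per cell | power per illness | exactly one significant |
|---|---|---|
| 63 | 0.951 | 0.093 |
| 72 | 0.972 | 0.054 |
| 90 | 0.991 | 0.017 |

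*(b) A continuous outcome such as the BDI.* The article gives no BDI effect or SD, so standardised effects d of 0.2 to 0.5 are assumed. Here p = Φ(d/√(2/n) − 1.96). Each entry is power per illness, then the chance that exactly one is significant.

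| n per cell | d = 0.2 | d = 0.3 | d = 0.4 | d = 0.5 |
|---|---|---|---|---|
| 63 | 0.201; 0.321 | 0.391; 0.476 | 0.612; 0.475 | 0.801; 0.318 |
| 72 | 0.224; 0.347 | 0.436; 0.492 | 0.670; 0.442 | 0.851; 0.254 |
| 90 | 0.268; 0.393 | 0.521; 0.499 | 0.765; 0.359 | 0.918; 0.150 |

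Simulation with 200,000 runs per setting agreed with these values. It gave a false-positive rate of 0.049-0.050 for the interaction test.

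**4. What the interaction test can detect.** The difference between two within-illness effects has SE = SD × √(4/n), which is 0.252, 0.236 and 0.211 SD at 63, 72 and 90 per cell.

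- Detectable with 80% power (× 2.80): 0.71, 0.66 and 0.59 SD.
- Detectable with 90% power (× 3.24): 0.82, 0.76 and 0.68 SD.
- Power if the effect is 0.5 SD in one illness and zero in the other (assumed): 51%, 56% and 66%.

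All these figures treat the outcome as one unadjusted measurement. They ignore baseline adjustment, repeated follow-ups and clustering by practice.

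**The case against.** Four arguments have weight.

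- **The article sets no faulty decision rule.** A reader might infer that the second objective will be decided on split p-values. The Analysis section does not link the separate analyses to that objective, and no section says how a difference or a generic effect would be declared. This stands. The defect is that no contrast is stated, and a wrong rule should not be attributed to the plan.
- **A check on effect modifiers is planned.** The checking is unconditional and only inclusion in the model is conditional. Together with stratification by illness, this leaves room for an interaction term, and a condensed article may leave model detail elsewhere. This stands in part. But the sentence concerns additional, unnamed factors, and the article does say how illness will be handled, namely separately. A named objective should not depend on a general check.
- **Separate analyses supply the ingredients of a test.** Two effects with their standard errors give the contrast as their difference divided by √(SE₁² + SE₂²), apart from some correlation through shared practices. This is correct. It would be too strong to say that the separate results could never be used to test a difference; the article does not say that the comparison will be made.
- **The risk of a false difference depends on the effect size.** A reader might infer that split results would mislead about half the time. The quantity 2p(1 − p) cannot exceed 50%, and it comes near that only when power per illness is near one half. At the article's own planning effect it is 2-9%, which at 72-90 per cell is about the interaction test's 5% or below. This stands, so a range must be given. The planning effect is binary with no events among controls, whereas the primary outcome is a BDI score, so neither basis settles the matter.

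**Conclusion.** The concern holds in limited form. The second objective is a between-illness comparison, the only illness-specific analyses stated are separate ones, and no contrast is named or powered. This is more than missing detail, because the handling of illness that the article does state does not answer the objective that it sets.

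With equal true effects, a reading based on separate p-values would suggest a spurious difference in about 2-9% of trials at the planning effect, and in about 15-50% for assumed BDI effects of 0.2-0.5 SD, both over 63-90 per cell. The interaction test holds this at 5%. The second range rests wholly on assumed effects. The documents do not support saying that a false difference will often appear, nor that the investigators intend to draw conclusions from split p-values.

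**What to change.** In the Analysis section, name the arm-by-illness interaction as the analysis for the second objective. Define illness by the randomisation stratum, fit the term in the multilevel BDI model on all patients, and report it with its 95% confidence interval. Keep the separate DM and COPD estimates as descriptive. State that neither a different nor a generic effect will be concluded from separate p-values.

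This costs one model term and a sentence or two. It needs no new data, since the stratification and the multilevel model are already in the plan. The article reports follow-up as still under way, so the analysis could be fixed before the data are complete.

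The downside is that the estimate will be imprecise, as the detectable differences above show. The text should therefore add that a non-significant interaction is not proof of a generic effect and that the confidence interval is to be read for the size of difference it leaves open.
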